**Patient**	
**Active interventions** *Painful Interventions Scale *[29]	Measures invasive hospital procedures shown to be moderately to severely painful or uncomfortable including arterial blood gas testing, mechanical ventilation, naso-gastric feeding and bladder catheterisation
**Other interventions**	i.e. Resuscitation status, PEG feeding, prescription of neuroleptics
**Quality of end of life care**	Prescription of analgesia at time of death, use of Liverpool Care Pathway
**Survival times**	Time of intervention to time of death
**System**	
**Advanced care planning**	Numbers choosing to make advanced care plan and adherence to advance care plan
**Readmission rates**	For emergency acute admissions
**Place of death**	
**Referrals**	To community palliative care
**Economic**	
**Service use costs **[30] Client Service Receipt Inventory (CSRI)	Baseline, 6 months and, if relevant, for the month prior to death

1) *Carer related *– such as stress and well being, general health and quality of life, satisfaction with the decision making process and a general measure of how they experienced the care planning process.

2) *Patient related *– to include measures of painful medical interventions i.e. intravenous cannulation, measurement of arterial blood gases), indicators of the quality of end of life care and survival time (intervention until death). These do not involve any burden to the patient and are gathered from routine clinical documentation.

3) *System-related *– for example adherence to the advanced care plan, referrals to and input from community palliative care, rates of unplanned hospital admission, and place of death.

4) *Economic measures *– differences between intervention and control groups may have an economic impact (positive or negative) in terms of health/social care resources used and also help provided by informal carers. Data on hospital stays will be obtained from administrative records.

#### Follow-up

The timing of patient and carer follow up assessments has been determined by the published evidence on survival time and prognosis for these patients (see Table 1). We will assess the feasibility of long term follow up i.e. whether reliable data can be collected about the care received at death. We will follow up patients and carers at 6 weeks from the index admission, at any subsequent hospital admissions and at 6 months from baseline. We aim to interview carers again three months after bereavement.

#### Data management and analysis

We shall use descriptive statistics to examine baseline data on proportions of carers agreeing to assessment and patients' demographic and clinical characteristics. Follow-up rates will be reported. Outcome measures, including clinical and health economic outcomes will be explored using descriptive statistics. Differences between the intervention and control groups will be investigated using regression methods to control for baseline characteristics. We will estimate the likely effect size of the intervention (additional to usual care) in order to guide a sample size calculation for a definitive phase III randomised trial. Economic factors will also be evaluated; unit costs [15] will be estimated for each of the study arms and the cost for each patient calculated. These will be linked to the short-term outcomes in the form of an incremental cost-effectiveness analysis that will enable us to make preliminary comparisons between the intervention and control groups in terms of the cost of achieving unit changes in outcomes. Cost comparisons between the two arms will be made using bootstrapping methods if data are skewed.

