**Design/Methods:**

We have used the MRC complex interventions framework, a "bottom-up" methodology, to develop an intervention for patients with advanced dementia and their carers aiming to 1) define end of life care needs for both patients and carers, 2) pilot a palliative care intervention and 3) produce a framework for advance care planning for patients.

The results of qualitative phase 1 work, which involved interviews with carers, hospital and primary care staff from a range of disciplines, have been used to identify key barriers and challenges. For the exploratory trial, 40 patients will be recruited to each of the control and intervention groups. The intervention will be delivered by a nurse specialist. We shall investigate and develop methodology for a phase 3 randomised controlled trial. For example we shall explore the feasibility of randomisation, how best to optimise recruitment, decide on appropriate outcomes and obtain data for power calculations. We will evaluate whether the intervention is pragmatic, feasible and deliverable on acute hospital wards and test model fidelity and its acceptability to carers, patients and staff.

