### Objectives

Our main objective is to assess the feasibility of implementing a palliative care needs assessment and advanced care plan for patients with advanced dementia who have been admitted to the acute medical ward.

We will ascertain which outcome measures are the most valid in this setting. We will also gather information on recruitment, the feasibility of randomisation and attrition in this cohort. We will obtain views from professionals and patients on the acceptability and practicality of delivering or receiving the intervention and monitor the consistency of its functional implementation.

Data will be used to generate the power calculation for a definitive trial and will provide estimates of recruitment rates, barriers to recruitment, the likely treatment effect and reasons for attrition.

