#### Patient recruitment

The research team will screen all admissions to two acute wards (intervention and control) and identify potential participants. We will monitor recruitment rates per month in relation to the total numbers of patient/carer dyads who would be eligible and detail reasons for those who decline to participate. We intend to recruit 40 patients and carers to the intervention arm and 40 patients and carers to the control arm. For an overview of measurements taken during the study, see Table 1.

**Table 1 T1:** Study schedule

**Measure**	**Source**	**Baseline**	**6 weeks**	**6 months**	**Subsequent hospital admission**	**Time of death**	**3 months post bereavement**

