#### Study procedures-Control arm

The patients and carers in the control arm will be recruited from an adjacent ward. They will be fully informed about the trial but there will be no change to usual care. Identical outcome measures will be used for both control and intervention groups. If the trial reveals areas of clinical need the MDT will be informed and this intervention documented.

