We shall use this pilot phase to evaluate whether the intervention is pragmatic and feasible within the challenging environment of NHS acute hospital wards. It will be enable us to determine which are the most effective and useful outcome measures and what may be the best measures of effectiveness; these may differ between the carer, potential benefit for the person with dementia and wider benefit to the health service. We do not know which aspect of the intervention will provide the active component that most influences change within this complex system. We envisage that to avoid "contamination" the future phase III trial will be clustered at hospital ward level. By defining key primary outcomes we will be able to generate data for a power calculation, which is vital as we anticipate that cluster randomisation will be the optimal methodology.

The preparatory work allowed us to explore ethical issues regarding research on subjects who do not have the capacity to give fully informed consent to participate. We used an ethics committee "flagged" to deal with research on subjects who lack the capacity to consent (under the terms of the recently enacted Mental Capacity Act) and will gain assent from their carers. We believe that this research brings a number of potential benefits as determined by the Act, for example "developing more effective ways of treating a person or managing their condition", "improving the quality of healthcare, social care or other services that they have access to" and "reducing the risk of the person being harmed, excluded or disadvantaged".

There are a number of methodological issues that still require consideration. We do not know what constitutes a good outcome in these patients with advanced dementia who are generally unable to express their needs and wishes. We will use the views of proxies which may not accurately reflect patients' wishes when they last had capacity.

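### With one ward per arm, the pilot's between-arm difference cannot be separated from the ward difference, so it should not be the planning effect for phase III

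*Protocol article*

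**What the plan says.** Under Patient recruitment, the article identifies participants by ward: "The research team will screen all admissions to two acute wards (intervention and control) and identify potential participants". The same section sets the size: "We intend to recruit 40 patients and carers to the intervention arm and 40 patients and carers to the control arm". Under Study procedures-Control arm it adds: "The patients and carers in the control arm will be recruited from an adjacent ward". No random allocation is described. The abstract lists it as a question for the study: "we shall explore the feasibility of randomisation".

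Under Data management and analysis, the comparison is defined as follows: "Differences between the intervention and control groups will be investigated using regression methods to control for baseline characteristics". The next sentence gives its use: "We will estimate the likely effect size of the intervention (additional to usual care) in order to guide a sample size calculation" for the definitive randomised trial. The Objectives say the same: "Data will be used to generate the power calculation for a definitive trial", and the likely treatment effect is listed there among the quantities to be provided.

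The Discussion expects that "the future phase III trial will be clustered at hospital ward level", in order to avoid contamination. It does not say that the pilot's own contrast is one ward against another, or that this limits the estimate.

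**The concern.** Ward and arm are the same variable. Baseline regression can remove differences in measured patient and carer characteristics. It cannot remove differences in ward practice or in unmeasured case mix. Several outcomes in Table 3 depend on practice during an admission: painful procedures, resuscitation status, neuroleptic prescribing, use of the end-of-life pathway and palliative referral. A ward difference in any of these would be read as intervention effect.

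What is at stake is the phase III sample size. Required size varies with the inverse square of the planning effect, so a modest ward difference in either direction can make the definitive trial much too small or needlessly large. A later analysis plan cannot repair this, because the limit lies in how the two arms are formed.

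**Working it through.** The 40 per arm is stated without power, effect size, SD or ICC, so there is no figure to reproduce. For a feasibility study that is not an error.

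**Inputs.** One ward per arm and m = 40 dyads per ward (Patient recruitment). The ward ICC, ρ, is not in the article; it is assumed here over 0.01 to 0.10. Effects are in units of the outcome SD.

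**Step 1: what the contrast estimates.** Contrast = intervention effect + residual ward difference. A ward term in the regression would be collinear with arm, and one ward per arm leaves no degrees of freedom for ward variance. Choosing by chance which ward receives the intervention would not change this.

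**Step 2: standard errors.**
- Patient-level SE = √(2/m) = √(2/40) = 0.224.
- SD of a pure ward difference = √(2ρ), which does not contain m.
- SE including ward variance = √(2(1−ρ)/m + 2ρ).

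| Assumed ρ | SD of ward difference | Patient-level SE | SE with ward variance |
|---|---|---|---|
| 0.01 | 0.14 | 0.224 | 0.264 |
| 0.02 | 0.20 | 0.224 | 0.298 |
| 0.05 | 0.32 | 0.224 | 0.384 |
| 0.10 | 0.45 | 0.224 | 0.495 |

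For example, at ρ = 0.02: √(0.049 + 0.040) = √0.089 = 0.298.

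**Step 3: precision with no ward effect.** The unadjusted 95% half-width is t(78) × √(2/40) = 1.991 × 0.2236 = 0.445. An observed 0.40 SD would run from about −0.045 to 0.845. Adjusting for a baseline score with an assumed correlation of 0.5 multiplies the half-width by √(1 − 0.25) = 0.866, giving about 0.39.

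**Step 4: consequence for phase III (illustration).** Assume a true effect of 0.3 SD, two-sided 5%, 80% power. With individual randomisation, n per arm = 2(1.96 + 0.842)²/0.3², about 175. Take ρ = 0.02 and a ward difference of one SD (0.20):
- In favour of the intervention, the contrast is 0.50 and n = 63 per arm. Power at the true 0.3 is then about 39%.
- Against it, the contrast is 0.10 and n = 1,570 per arm.

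These sizes are for individual randomisation. In a ward-clustered trial with a fixed number of patients per ward, each is multiplied by the same design effect. The ratios therefore stay: (0.3/0.5)² = 0.36 and (0.3/0.1)² = 9 times the correct size.

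**The case against.** The study is declared exploratory, and its main objective is feasibility. No efficacy claim or go/no-go rule rests on the contrast. Recruitment, acceptability, attrition and choice of outcomes are unaffected. All of this stands, and the two-ward design is acceptable for those aims.

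The wards are adjacent, in one hospital, with the same eligibility criteria and the same measures. Some outcomes are collected weeks or months later, when ward influence may be weaker. So the residual ward difference may be small, and its direction is unknown. That is fair, but the pilot cannot show that it is small.

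The article speaks of guiding a calculation, which leaves room for other evidence. That softens the point, but the Objectives state more directly that the pilot data will generate the power calculation and provide the likely treatment effect.

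Stronger readings are tempting and are not supported:
- A reader might infer that the planned interval is too narrow or that a planned 5% test has an inflated error rate. The article states no between-arm interval or test. Any such error rate would rest wholly on an assumed ICC.
- A reader might infer that phase III could be wrongly abandoned. No abandonment rule exists.
- A reader might infer that the pilot should randomise within wards or swap the wards' roles. The article is concerned about contamination, and the nurse discusses problems with the clinical team and records plans in the notes. Either change would trade one difficulty for another.

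**Conclusion.** The point holds in limited form. The complete overlap of ward and arm follows from the text alone and needs no assumption. So does the conclusion that baseline regression cannot isolate the intervention effect. The contrast is therefore not a valid planning effect for phase III, although the Objectives and the analysis section give it that role.

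The size depends on an assumed ICC. Over 0.01 to 0.10, any patient-level SE leaves out a ward component with an SD of 0.14 to 0.45, which more patients per ward would not reduce. The half-width of about 0.445 SD with no ward effect needs no ICC, but it is unadjusted and would be somewhat smaller with the planned adjustment. The phase III figures in Step 4 are illustrations, not predictions.

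This is a correction to the stated use of one estimate. It does not show that the pilot is unfit for its feasibility purpose or that it should not proceed.

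**What to change.** Change the effect-size sentence under Data management and analysis, and the matching statement under Objectives, to say that:
- arm differences will be reported as descriptive, with 95% confidence intervals, and with a statement that they cannot be separated from the difference between the two wards;
- they will not be used as the planning effect for phase III;
- phase III will be sized on a minimum important difference for the chosen primary outcome;
- the pilot will supply the SD, control-ward event rates, baseline-to-follow-up correlation, recruitment and retention;
- the ward ICC, which the expected ward-clustered design needs, will come from external data or an assumed range, because one ward per arm cannot supply it.

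The cost is wording, and a slightly less ambitious purpose for the pilot. Some work is also needed to justify a minimum important difference, since the Discussion accepts that it is not yet known what a good outcome is for these patients. Recruitment, allocation and delivery of the intervention stay as planned.

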#### Ethical issues

By definition, this research will be carried out on subjects who are unable to give informed consent. Our study was approved by the ethics committee of Camden and Islington Mental Health and Social Care Trust (London, UK). This ethics committee is "flagged" to consider research on those unable to consent for themselves, as described in Section 30 of the Mental Capacity Act 2005. We believe that the risk to patients and carers is negligible and this project does not involve any invasive procedures. We will consult and seek assent from the carers and any other relevant people as defined by section 32 of the Mental Capacity Act (2005) code of practice. As we will be measuring the impact of the intervention on specific carer outcomes we will seek fully informed consent from the carer for their own participation as a subject.

## Discussion

Patients with advanced dementia have complex physical and psychological needs. They are different to many other terminally ill patients in that they have severe impairment of basic activities of daily living and may lack capacity to make appropriate decisions regarding their choices and preferences at the end of life. Assessing needs at the end of life and planning care is a complex issue and, in people with advanced dementia, much of this may be done by proxies. These difficulties are further increased by the healthcare system. People with advanced dementia may reside in nursing homes and at the same time be under the care of acute hospitals, community mental health teams and clinical staff from a range of specialities spanning primary and secondary care. This complicated care system makes adequate communication between care providers, patients and their carers very challenging.

We have used the MRC complex interventions framework to move from our earlier theoretical work to pilot an intervention that aims to address the issues described above. The findings from the qualitative phase were vital in investigating and teasing out the important "ingredients" of an intervention. It highlighted challenges to improving end of life care for this patient group. In particular, it demonstrated a widespread lack of understanding of the natural history of dementia and its progression. This suggests that education and advanced care planning discussions should be at the centre of an intervention. Benefits may extend to improved understanding, more appropriate decision making and thereby reductions in un-necessary hospitalisations as well as more appropriate end of life care for patients with advanced dementia. It may also lead to greater satisfaction with end of life care and better bereavement outcomes in relatives.

We shall use this pilot phase to evaluate whether the intervention is pragmatic and feasible within the challenging environment of NHS acute hospital wards. It will be enable us to determine which are the most effective and useful outcome measures and what may be the best measures of effectiveness; these may differ between the carer, potential benefit for the person with dementia and wider benefit to the health service. We do not know which aspect of the intervention will provide the active component that most influences change within this complex system. We envisage that to avoid "contamination" the future phase III trial will be clustered at hospital ward level. By defining key primary outcomes we will be able to generate data for a power calculation, which is vital as we anticipate that cluster randomisation will be the optimal methodology.

The preparatory work allowed us to explore ethical issues regarding research on subjects who do not have the capacity to give fully informed consent to participate. We used an ethics committee "flagged" to deal with research on subjects who lack the capacity to consent (under the terms of the recently enacted Mental Capacity Act) and will gain assent from their carers. We believe that this research brings a number of potential benefits as determined by the Act, for example "developing more effective ways of treating a person or managing their condition", "improving the quality of healthcare, social care or other services that they have access to" and "reducing the risk of the person being harmed, excluded or disadvantaged".

There are a number of methodological issues that still require consideration. We do not know what constitutes a good outcome in these patients with advanced dementia who are generally unable to express their needs and wishes. We will use the views of proxies which may not accurately reflect patients' wishes when they last had capacity.

It could be argued that much of what comprises this intervention is just good quality care and should be part of routine clinical practice; it is too much like what professionals believe they "do already". Naturally, some elements of the intervention will occur in usual care, although all the evidence published to date suggests that it is rarely carried out in a consistent manner. Furthermore, this sort of concern hardly ever interferes with a careful, controlled evaluation [16]. In addition to evaluating the intervention itself, we will also assess its implementation in terms of change management within a complex health [17] system.

The results of our study may have wider implications, particularly with regards to palliative care interventions in neurodegenerative disease and conditions other than cancer where patients may lack capacity and the disease trajectory is not easy to predict.

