#### Study setting

The study is set on acute medical wards for people over the age of 70 years in the Royal Free Hospital NHS Trust, a large inner London teaching hospital serving an inner city population that is diverse in terms of socioeconomic and ethnic mix.

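### With one ward per arm, the pilot cannot supply the between-ward variance, or an effect size free of ward differences, for the ward-clustered trial it is meant to help size

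*Protocol article*

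**What the plan says.** Three places in the protocol article describe how the pilot is to inform the later trial.

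- Objectives: "Data will be used to generate the power calculation for a definitive trial". The same sentence lists the likely treatment effect among the quantities to be estimated.
- Data management and analysis: arms are compared by regression adjusted for baseline characteristics, and the resulting effect size is to guide the phase III sample size.
- Discussion: the authors envisage that "the future phase III trial will be clustered at hospital ward level", in order to avoid contamination. They add that, once key primary outcomes are defined, "we will be able to generate data for a power calculation, which is vital as we anticipate that cluster randomisation will be the optimal methodology".

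Elsewhere the pilot's structure is fixed. It takes place in one hospital (Study setting). Under Patient recruitment, "The research team will screen all admissions to two acute wards (intervention and control) and identify potential participants", and "We intend to recruit 40 patients and carers to the intervention arm and 40 patients and carers to the control arm". Under Study procedures-Control arm, "The patients and carers in the control arm will be recruited from an adjacent ward".

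The article does not mention an intracluster correlation, a between-ward variance, a design effect or an outside source for any of them.

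**The concern.** A trial randomised by ward needs two inputs beyond those of an individually randomised trial: the number of patients per ward and the ICC. The Discussion gives the expected cluster design as the reason why the pilot's power-calculation data matter. With a single ward in each arm, however, the clustering parameter is exactly what this design cannot yield.

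A second input is affected as well. The pilot's effect size is a contrast between two wards, so it contains any difference between them in staffing, case mix or practice as well as the effect of the intervention. Adjusting for patients' baseline characteristics can remove measured differences in case mix. It cannot separate ward from intervention.

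If the Objectives and the analysis section were followed as written, with nothing brought in from outside, a ward-clustered trial would be sized from a ward-confounded effect and with no between-ward variance.

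**Working it through.** The article gives 40 dyads per arm without alpha, power, effect size, SD or ICC, so there is no derived figure to reproduce.

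**Step 1: can the ICC be estimated?** This step uses document inputs only: 2 wards (Patient recruitment), 2 arms, and controls from one adjacent ward (Study procedures-Control arm).

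- Between-ward degrees of freedom = wards − arms = 2 − 2 = 0.
- For 80 patients, 40 per ward, the design matrix with intercept and arm has rank 2. Adding the two ward indicators leaves the rank at 2, so ward is completely aliased with arm.
- Once arm is fitted, the ward component in the residual contrasts is zero (largest element about 4 × 10⁻³¹, which is rounding error). The within-arm data carry no information on between-ward variance, and more patients per ward would not change this.

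**Step 2: what happens to the effect estimate?** In units of the total SD, with one ward of 40 in each arm, the variance of the difference is 2 × [ICC + (1 − ICC)/40] = (2/40) × (1 + 39 × ICC). A patient-level regression sees only the within-ward part, 2 × (1 − ICC)/40. The ICC values are assumed.

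| ICC | True SE | SE a patient-level regression would report |
|---|---|---|
| 0 | 0.224 | 0.224 |
| 0.01 | 0.264 | 0.222 |
| 0.05 | 0.384 | 0.218 |
| 0.10 | 0.495 | 0.212 |

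The reported SE stays between 0.21 and 0.22 whatever the ICC, and nothing in the data would reveal the discrepancy.

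**Step 3: how far does an unknown ICC move a phase III size?** This step is illustrative. The standardised effect d = 0.3, 90% power, two-sided 5%, the number per ward m and the ICC range are all assumptions. The value m = 40 borrows the pilot's recruitment target per arm; the article gives no phase III ward size.

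- Individually randomised n per arm = 2 × [(1.96 + 1.2816)/0.3]² = 233.5.
- Design effect = 1 + (m − 1) × ICC.

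| m | ICC | Design effect | n per arm (rounded up) |
|---|---|---|---|
| 40 | 0.01 | 1.39 | 325 |
| 40 | 0.10 | 4.90 | 1,145 |
| 10 | 0.01 | 1.09 | 255 |
| 10 | 0.10 | 1.90 | 444 |

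The spread is 4.90/1.39 ≈ 3.5-fold at m = 40 and 1.90/1.09 ≈ 1.7-fold at m = 10.

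**The case against.** The strongest reply is that the article never promises an ICC. The Discussion speaks of data for a power calculation, which need not mean every input. Outcome SDs, event rates, recruitment and attrition are needed for a cluster calculation too, and the pilot can provide them. The firmer wording in the Objectives refers to a definitive trial without mentioning clustering. Taking an ICC from elsewhere is compatible with every sentence. A condensed article may also properly leave the source of an ICC to a fuller document, so its absence alone would be no finding. The phase III design is only envisaged and its primary outcome is not chosen. Finally, a pilot with a few wards per arm would still estimate an ICC very imprecisely, so this is not a flaw that a modest redesign would cure.

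Most of this stands, and it rules out three stronger readings that a reader might infer:

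- *That the authors will in effect set the ICC to zero and under-size phase III.* Nothing in the article says that phase III will be sized from pilot data alone. The authors plainly have clustering in mind.
- *That the ICC is the dominant planning parameter.* This is not shown. Moving d from 0.3 to 0.5 changes n by (0.5/0.3)² ≈ 2.8-fold, which is more than the ICC spread at m = 10.
- *That the pilot cannot inform the sample size at all.* It can, for the inputs named above.

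The reply does not remove the mismatch between stated purpose and design. The Objectives make the pilot the source of the power calculation, the Discussion ties the value of those data to cluster randomisation, and neither states the limit. Nor does the reply touch the effect size. The analysis section says expressly that it will be carried forward, and it is confounded with ward whatever source is used for the ICC.

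**Conclusion.** The point holds in a limited form. The article states a deliverable that its two-ward design cannot fully supply. That conclusion rests only on the number of wards and arms and needs no assumed figure. The illustrated sample sizes, by contrast, depend wholly on the assumed effect, power, ward size and ICC range, and show only that the missing input can matter.

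Severity is moderate. The main objective, feasibility of the needs assessment and care plan, is unaffected, and any consequence would arise in a later trial with its own sample-size justification.

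**What to change.** Change the wording in three places.

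1. Objectives and Discussion: state that the pilot will not estimate the ICC or between-ward variance, and that its inputs to the phase III calculation are within-ward SDs, event rates, recruitment and attrition.
2. Data management and analysis: state that the estimated effect is confounded with the difference between the two wards and that its patient-level standard error excludes between-ward variation. It should therefore not be used as the phase III effect size.
3. Discussion: state that a ward-clustered phase III will be sized over a stated ICC range (for example 0.01 to 0.10). The range should come from external estimates or, for record-based outcomes such as unplanned admissions, place of death and palliative care referral, from routine data on several comparable wards.

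The cost is a weaker stated claim for the pilot and, optionally, a small extract of routine ward data. No extra patients are needed.
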